### Real-Time Daily Data Collection

SMS text messaging survey data will be collected using the “survey as a text conversation” feature in REDCap [48,49], which mimics a typical SMS text messaging conversation where questions are sent one-at-a-time and each question is sent only after a response is received. Surveys will automatically close after completion or after 3 hours if no response is received, and the next survey will automatically be sent at the prescheduled time. SMS text messaging was selected for daily surveys based on discussions with T1DYAC members, the high prevalence of smartphone use among US teens (95%) [58], and high rates of smartphone initiation by the age of 12 years (75%) [59]. In addition, the daily and end-of-day surveys were designed to have no more than 10 questions at a time to reduce the overall participant burden.

Beginning after the baseline survey is completed, participants will receive SMS text messaging survey invitations 4 times per day on a fixed schedule in the morning (10 AM), afternoon (2 PM), early evening (6 PM), and end-of-day (10 PM) [3] The morning, afternoon, and early evening surveys focus on interactions with their diabetes technology, challenges in managing diabetes, and other events that have occurred in the last few hours. For example, 1 question asks, “What have you been doing in the last few hours (ie, exercising, eating, at school, etc)?” In the evenings (10 PM), participants will complete a guided reflection using open-ended questions. During the reflection, they will be asked to open their diabetes device app and review the graph of their glucose levels throughout the day. Qualitative and quantitative data will be integrated during data collection as participants provide written reflections on their CGM data in daily SMS text messaging surveys. In addition, they will share information about what activities they did that day and how they feel events and activities impacted their diabetes. For example, the first question asks, “Overall, how did you feel about your diabetes today?” Sample daily and end-of-day survey question items and their alignment with the COM-B model can be found in Table 1. Complete daily and end-of-day SMS text messaging surveys are included in Multimedia Appendix 3. Participant response rates will be tracked automatically by REDCap throughout the study. In addition, participants will complete an open-ended text messaging survey after the 30 days of daily surveys are completed to qualitatively share their study experiences, burden, and study acceptability.

During the same 30 days, participants will be asked to continue CGM as prescribed to collect glucose levels. Depending on the device manufacturer, glucose levels are measured automatically every 1 to 15 minutes. By not introducing a new device, reactivity is reduced, and we are able to capture typical self-management behaviors and glycemic levels in this population. Likewise, participants do not have to learn to use a different device solely for the purpose of this study. Glycemic data are not blinded from participants to maintain normalcy with their daily routine and to maintain their safety in managing potentially dangerous high and low glucose levels during the study period. After completion of the daily survey portion of the study, participants will receive a secure REDCap survey link to share their CGM data from the previous 30 days downloaded as a .csv file from their CGM platform (eg, Dexcom Clarity). In addition, participants will be asked to reflect on the feasibility and acceptability of the study through 7 survey questions. Questions include study barriers, facilitators, and reflections on the length and timing of data collection (see Multimedia Appendix 4 for full closeout survey).

### Semistructured Interview

A subsample of participants (n=20‐30) will be invited to complete a 1-hour follow-up interview with a member of the study team trained in qualitative data collection and analysis. A maximum variation sampling approach will be leveraged and rely on recent HbA_1c_ levels, baseline survey scores, age, gender, race or ethnicity, diabetes duration, and diabetes device use as well as responses to the SMS text messaging surveys. Interviews are intended to further explore their approach to self-management using their diabetes devices. Interview prompts will focus on the participants’ daily approach to managing their diabetes, including decision-making, problem-solving, and interactions with technology. Alignment of interview prompts with the COM-B model is described in Table 1. Likewise, a portion of the interview will be dedicated to exploring study feasibility and acceptability, including perceived study burden and experiences of behavior change during the study period. Interviews will be conducted using Health Insurance Portability and Accountability Act (HIPAA)-compliant web conference tools (eg, Zoom; Zoom Communication, Inc), audio-video recorded, and transcribed for analysis. In line with a traditional qualitative approach, analysis and data collection will be completed simultaneously, and the final sample size will be determined by theoretical saturation.

### Analytic Approaches

### Overview

Qualitative (open-ended survey responses and interview transcripts) and quantitative (baseline survey and CGM) data will be analyzed simultaneously and integrated to address the study aims. For aim 1, we will use a constructivist grounded theory approach, integrating findings from the daily survey and interview data with CGM and psychosocial measures. For aim 2, we will use a descriptive approach, integrating findings from the closeout survey and follow-up interview to assess feasibility and acceptability. Figure 3 summarizes the analysis and integration plan across data sources.

**Figure 3. F3:**
[figure not shown]
Overview of data analysis and integration plan. Red, blue, and purple colors indicate qualitative, quantitative, and mixed analyses, respectively. CGM: continuous glucose monitoring; T1D: type 1 diabetes.

#### Qualitative Analysis

A .csv file with daily, end-of-day, and closeout survey responses will be downloaded from REDCap for each participant. Columns will include survey timing (eg, morning and afternoon) and study day followed by a column for each survey question. Each row will include responses from a unique survey instance. Interview transcripts and .csv files will be imported and grouped by participant within qualitative and mixed methods data analysis software to support data management (eg, MAXQDA [Max Weber Qualitative Data Analysis]; VERBI GmbH). Participant summaries will be created to merge all data by participant (see also “Mixed Methods Integration” section).

Following a constructivist grounded theory approach informed by Charmaz [42], the principal investigator and research team members will perform at least two iterative rounds of line-by-line coding on the qualitative data: (1) initial coding to identify concepts that are important to participants; and (2) focused coding to synthesize concepts and identify patterns across participants. Theoretical coding can be used to further examine relationships between codes to construct a theory grounded in participant experiences [42]. Throughout the grounded theory analysis, a hybrid inductive-deductive approach will be leveraged, incorporating domains from the COM-B model alongside those identified from participant responses [60] to assist in identifying critical self-management behaviors as they relate to diabetes device use. Findings will be presented as a theory of optimal advanced diabetes technology use for self-management, grounded in the experiences and perspectives of adolescents with T1D. We will refer to COREQ (Consolidated Criteria for Reporting Qualitative Research) guidelines Checklist 1to ensure rigor and transparency in reporting [61].

Due to the frequency of data collection in our approach, we anticipate that not all questions will be answered in the real-time daily surveys. We will look for patterns of missing data within and across participants to identify any systematic issues in data collection that may influence analysis and interpretation [62]. Otherwise, any missing data will be treated as a nonresponse. Due to the longitudinal nature of data collection, we anticipate having sufficient responses across daily survey and interview data to reach theoretical saturation. However, additional data collection will occur as needed to further refine the theory [42].

#### Quantitative Analysis

Baseline survey metrics and clinical characteristics collected from medical records (eg, HbA_1c_) and participant response rates will be summarized using descriptive statistics. In line with the adapted STROBE (Strengthening the Reporting of Observational Studies in Epidemiology) Checklist for Reporting EMA Studies (CREMAS) from Liao et al [63], we plan to report participant attrition rates according to study days, response latency, overall and daily compliance rates (total responses per participant and average number of responses), and associations of compliance with demographic, clinical, and other time-varying variables.

In this mixed methods study, quantitative measures will be used to characterize the sample and expand understanding of each participant’s experience when integrated with qualitative findings. CGM-derived metrics of glycemic control will include those recommended by consensus guidelines from Battelino et al [64] such as sensor use time, time in ranges (ie, above and below), and the glucose management indicator. A minimum of 14 days of CGM data with sensor use 70% of the time has been previously established as sufficient for analysis. The *iglu* R package (R Foundation for Statistical Computing) [65,66] will be used to process and analyze all collected CGM data, and interpolation will be used for small windows of missing data (eg, 45 min). Additional analysis packages (eg, *Best Linear IMPutation*) will be used to impute expected longer periods of missing data (ie, periods of signal loss and sensor malfunction) to reduce bias introduction and evaluate the randomness of missing data and impute missing values, where appropriate [67].

To test for mean differences in psychosocial and behavioral characteristics between glycemic level groups (HbA_1c_>9% and those with HbA_1c_≤9%) at baseline, 1-tailed *t* tests will be used. If the data are nonparametric, appropriate alternative tests (ie, the Wilcoxon rank paired test) will be performed. For all participants with at least 28 days of continuous glucose data, we will use linear mixed models to identify risk factors that influence blood glucose levels, model changes in blood glucose over time, and test any intervention effect resulting from longitudinal data collection. Additional statistical tests may be performed as appropriate based on the data collected. Statistical analysis will be performed on the data of all included study participants, and a statistical significance level of 5% (α=.05) will be used to test for differences and associations.

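### Imputing long CGM gaps with a linear fill distorts time in range and variability even when gaps are random; these metrics should rest on observed readings

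*Protocol article*

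**What the plan says.** All the relevant text is in the Quantitative Analysis section.

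- **Metrics.** The CGM outcomes are consensus metrics "such as sensor use time, time in ranges (ie, above and below), and the glucose management indicator".
- **Short gaps.** Small windows, with 45 minutes as the example, are interpolated.
- **Long gaps.** Further packages, with Best Linear IMPutation as the example, "will be used to impute expected longer periods of missing data". The causes named are "periods of signal loss and sensor malfunction". The stated purpose is "to reduce bias introduction and evaluate the randomness of missing data and impute missing values, where appropriate".
- **Sufficiency.** "A minimum of 14 days of CGM data with sensor use 70% of the time has been previously established as sufficient for analysis".
- **Mixed models.** These are planned "For all participants with at least 28 days of continuous glucose data".

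Nothing restricts long-gap imputation to analyses that need a complete series. Nothing says whether the metrics, the 70%/14-day rule or the 28-day threshold are computed before or after filling.

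**The concern.** Time in range is the share of readings between two cut-offs. A best linear fill replaces each missing reading by its expected value given the neighbouring data. Well inside a long gap, that value settles near the person's usual level for the time of day. Real glucose would have crossed the cut-offs repeatedly, but the filled stretch lies almost wholly on one side. Highs, lows and spread are lost. This happens even if gaps occur completely at random, when observed readings alone would give a nearly unbiased proportion. The step adopted to reduce bias can therefore create it.

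The Mixed Methods Integration section puts CGM metrics and ambulatory glucose profiles into each participant summary, next to real-time survey replies. Its joint displays are meant to help explain glycemic levels and variability. A filled stretch could be read there as real glucose, with its variability removed. In the mixed models, a single fill treated as data would count readings that were never taken. Likelihood-based mixed models do not need filled gaps when data are missing at random.

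**Working it through.** The article states no CGM bias, power or variability figure, so there is nothing to reproduce. Glucose inputs below are assumptions; range is 70-180 mg/dL.

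**Inputs from the article.** CGM use near 70% (Abstract, Results) or sensor use above 75% (Results), so about 25-30% missing. Eligibility allows 20 days per month, so up to 10/30 = 33% of days without CGM. Not all of this is signal loss or malfunction, so 30% is the upper end and 10% is also shown.

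**1. Truth.** For roughly normal glucose with mean m and SD s, time in range = Φ((180 − m)/s) − Φ((70 − m)/s).
- m = 160, s = 60: Φ(0.333) − Φ(−1.5) = 56.4%.
- m = 235, s = 85: Φ(−0.647) − Φ(−1.941) = 23.3%.

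**2. Limiting case.** With very long gaps the fill equals the mean, so the gap counts as 100% in range for m = 160 and 0% for m = 235. At 30% missing:
- 0.7 × 56.4 + 0.3 × 100 = 69.5%.
- 0.7 × 23.3 + 0.3 × 0 = 16.3%.
- SD is multiplied by √0.7 = 0.837, a fall of 16%.

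**3. Finite gaps.** Take a 15-minute grid, correlation time 2.5 h, ρ = exp(−0.25/2.5). In a gap of n readings the filled value at position k has variance s²R²(k), where R²(k) = [ρ^(2k) + ρ^(2(n+1−k)) − 2ρ^(2(n+1))] / [1 − ρ^(2(n+1))]. Put s√R²(k) into the formula in step 1, average over k, and weight by the missing share.

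| Missing | Gap | m = 160 (true 56.4) | m = 235 (true 23.3) | SD |
|---|---|---|---|---|
| 30% | 3 h | 58.9 | 21.9 | −6.5% |
| 30% | 6 h | 61.0 | 20.0 | −10% |
| 30% | 12 h | 64.9 | 18.0 | −13% |
| 30% | 24 h | 67.2 | 17.1 | −15% |
| 10% | 3 h | 57.2 | 22.8 | −2% |
| 10% | 12 h | 59.2 | 21.5 | −4% |

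Simulation with these inputs and 12-hour gaps at 30% gave 66-67% and 18%, SD down 11-16% over 6- to 24-hour gaps, and time below range down by about a quarter or more. Observed-only values stayed within 0.7 points of truth. The fill leaves the mean about right when gaps are random, so the damage is to threshold and spread metrics.

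**4. With a time-of-day profile.** A person-level profile fill at 30% missing in 12-hour gaps moved time in range from 54.7 to 59.4 and from 23.9 to 19.3, with SD down about 13%.

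A further simulation used CV 40%, random gaps of 2-24 h, 30% missing and 40 people per group. It compared filling from each person's own profile with filling from a profile pooled over everyone:

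| Group means | Lower group: true / own / pooled | Higher group: true / own / pooled | Contrast: true / own / pooled |
|---|---|---|---|
| 165 v 250 | 62.3 / 65.5 / 50.3 | 26.0 / 19.2 / 20.0 | 36.2 / 46.3 / 30.3 |
| 155 v 230 | 67.9 / 72.9 / 61.5 | 32.2 / 24.0 / 28.7 | 35.8 / 48.9 / 32.7 |
| 190 v 250 | 51.6 / 49.5 / 40.2 | 24.6 / 18.0 / 18.4 | 27.0 / 31.5 / 21.8 |
| 200 v 270 | 45.9 / 39.6 / 34.3 | 20.1 / 14.8 / 15.0 | 25.8 / 24.8 / 19.3 |

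Observed-only levels were within 0.4 points of truth in all eight cells. Own-profile shifts run from 2.1 points (51.6 to 49.5) to 8.2 (32.2 to 24.0); pooled shifts reach 12.0 (62.3 to 50.3). At 10% missing, own-profile shifts were 0.9 to 2.9 points. Monte Carlo noise between scenarios is about 1-2 points.

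**5. Gaps that depend on glucose.** With 25-30% missing concentrated in high-glucose periods, observed-only time in range was too high by 5.1 points (19.9 to 25.0) to 9.8 points (46.6 to 56.4). For 165 v 250 at 30%, truth was 62.9 and 25.3, observed-only 72.1 and 32.4, own-profile fill 76.5 and 23.6, pooled fill 62.6 and 28.8. Neither approach is safe throughout, and filling was sometimes closer.

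**The case against.** **The algorithm is not described.** Best Linear IMPutation is only an example and the cited source is not at hand. This stands: the sizes apply to a single conditional-mean fill, and a stochastic method would behave differently.

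**The plan has safeguards.** It will assess randomness and impute only where appropriate. This helps little, because the distortion arises in the random case, which such a check would pass.

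**The sizes are an upper range.** Imputation is tied to signal loss and sensor malfunction, and non-wear is not named. With 10% missing, or gaps of about 3 hours, shifts are small. This stands.

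**Observed readings can be biased too.** This also stands (step 5), and it is why imputation should stay as a sensitivity analysis.

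**Stakes are modest.** Quantitative measures describe the sample and support a grounded theory; no confirmatory time-in-range test is planned. This stands.

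Three stronger readings are tempting but unsupported:

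- **That the plan hides true sensor wear.** The article never says wear is counted on a filled trace. If it were, 70% would read as 100%; counted from raw readings, it is unchanged. Only the order of operations is unstated, and the same holds for the 14-day and 28-day rules.
- **That filling exaggerates the difference between HbA1c groups.** An own-profile fill widened the contrast when means straddled 180 mg/dL and slightly narrowed it at 200 v 270; a pooled fill narrowed it in every random-gap scenario. The planned HbA1c-group tests concern psychosocial and behavioral measures, not CGM metrics.
- **That mixed-model standard errors will be materially too small.** The direction is plausible, but the size was not computed. If the 28-day rule counts observed days, at most 2/30 = 6.7% of days are wholly absent.

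**Conclusion.** The point holds in this limited form. The plan commits to imputing long CGM gaps as a way to reduce bias and does not exclude threshold metrics. If the fill is a single linear one, time in, above and below range and variability are distorted even under purely random missingness, where observed readings are nearly unbiased.

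Under the assumed glucose parameters the shift is roughly 3 to 10 points at 30% missing in long gaps, a little less in one own-profile setting and up to 12 with a pooled fill. At 10% missing it is about 0 to 3 points with person-level filling. SD falls by about 11-16% at 30% missing in 6- to 24-hour gaps. Group contrasts can move in either direction. These sizes rest on the assumed means, spread, correlation time and gap lengths, and on the fill being a conditional mean. The change is worth making because it is nearly free, not because a main conclusion is known to be at risk.

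**What to change.** In the Quantitative Analysis section, state that:

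- sensor use, the 70%/14-day and 28-day rules, time in ranges, the glucose management indicator and the ambulatory profiles are computed from observed readings, plus only the short interpolation of about 45 minutes;
- the linear mixed models are fitted to observed readings;
- imputation of longer gaps is a sensitivity analysis, using several stochastic draws that carry imputation uncertainty, reported beside the observed-data result;
- the share of missing or imputed time is reported by HbA1c group.

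**Cost.** A few sentences and no new data. Participants with much missing wear are summarised on fewer readings. Observed-only values are also biased if gaps depend on glucose, so the sensitivity analysis should always be shown with them.

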### Baseline Survey

Study participants will complete a one-time baseline survey. Measures were selected to align with components of the COM-B model and the literature on psychosocial influences on self-management and diabetes device use. The survey includes measures of diabetes self-management behaviors, depression, diabetes distress, attitudes towards diabetes technology, problem-solving, and self-efficacy with diabetes self-management. A summary of survey instruments, sample items, and their alignment with the COM-B model is included in Table 1. Additional details can be found in Multimedia Appendix 2.

**Table 1. T1:** Alignment of capability, opportunities, and motivation of behavior (COM-B) model with select data collection measures.

COM-B construct	Baseline survey items	Daily and end-of-day survey items	Semistructured interview questions
Capability (physically and psychologically able, including knowledge, decision-making, and skills)	Self-efficacy for T1D^a^ management: “[Can you…] adjust your insulin or food accurately based on how much exercise you get.” [50]. CGM^b^ self-efficacy: “I am sure I can... adjust insulin dose based on real-time data” [51].	Did you look at information from your diabetes devices in the last few hours? If no, why not?	What do you consider to be a high blood sugar? Why is this number significant to you?
Opportunity (social and environmental conditions, including social support and structural factors)	Clinical characteristics: For how long have you used CGM? How many days in the last month did you wear a CGM sensor or use CGM?	What problems, if any, did you encounter today? Were your diabetes devices useful to you today? How?	What support do you get from your health care providers that help you to use your technology?

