## Results

This study was reviewed and approved by the institutional review board in January 2025 and enrolled its first participant in April 2025. As of December 2025, 25 participants have enrolled in this study, and we anticipate meeting our enrollment goal of approximately 30 to 40 participants in early 2026. We anticipate findings to become available in the following several years through conference presentations and peer-reviewed publications. Furthermore, findings will inform the development of an intervention to address diabetes self-management and decision-making in adolescents with T1D.

Few previous applications of real-time data collection have leveraged conversational SMS text messaging (where questions are sent one-at-a-time following participant responses), and, as such, there is little data on participant burden and compliance available for this method; however, early studies using closed-ended surveys indicate high satisfaction and compliance rates (≤95%) among adolescents and young adults [74], especially when fewer prompts were used [75,76]. As a result, our study incorporated several recommendations for burden reduction and compliance optimization such as working with a population that feels connected to our study objective, using shorter, less frequent prompts, allowing a window of 2+ hours for responses, allowing the use of participants’ own devices, providing a monetary incentive after completing the study, and co-developing surveys with youth with lived experience of T1D from the T1DYAC [77,78]. As a result, we are hopeful for response rates of at least 70% in this study. Likewise, we expect themes emerging from the analysis of feasibility and acceptability responses to highlight overall participant satisfaction and low burden.

We anticipate that sensor use time will be above 75%, as this population will already use CGM prior to study enrollment. In addition, we anticipate that participants with HbA_1c_ of more than 9% will report lower problem-solving, self-management behaviors, and diabetes device use, and higher diabetes distress and depression compared with those with HbA_1c_ of 9% or less.

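### Baseline group comparisons are set as one-tailed t tests at 5%, but the article states an expected direction for only four of the eight scales it shows, and no difference opposite to the tested tail can be declared.

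*Protocol article*

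**What the plan says.** Under Quantitative Analysis, the article sets out its group comparison: "To test for mean differences in psychosocial and behavioral characteristics between glycemic level groups" (HbA1c above 9% versus 9% or less), "at baseline, 1-tailed *t* tests will be used". The same paragraph gives one error level for everything: "a statistical significance level of 5% (α=.05) will be used to test for differences and associations". It names no tested direction, for any scale.

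The only statement of direction is in the Results section. It anticipates that participants above 9% "will report lower problem-solving, self-management behaviors, and diabetes device use, and higher diabetes distress and depression" than the other group.

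The Baseline Survey section describes what is measured: "The survey includes measures of diabetes self-management behaviors, depression, diabetes distress, attitudes towards diabetes technology, problem-solving, and self-efficacy with diabetes self-management". Table 1 shows the instruments behind these constructs, with two separate self-efficacy instruments and two on attitudes to technology or CGM.

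**The concern.** A one-tailed test needs a direction fixed before the data are seen. The article prescribes the test for the whole class of psychosocial and behavioral characteristics but supplies directions for only part of it. This has two consequences.

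- **Scales without a direction.** The analysis cannot be carried out as written. Someone must choose the tail later. If the observed means guide that choice, the real error rate of the test is double the nominal rate.
- **Scales with a direction.** A difference of the opposite sign cannot be called significant, however large it is.

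The second consequence matters because aim 1 is to build a theory, not to confirm a known ordering of the groups. The Introduction reports both satisfaction among regular CGM users and alarm fatigue, mistrust of readings and a burden that can add to distress. An unexpected sign on distress is therefore not far-fetched.

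**Working it through.** **Inputs**

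- Test and level: one-tailed t test, α = 0.05 (Quantitative Analysis).
- Scales: the baseline instruments in Table 1 (Baseline Survey).
- Directions: the Results section.
- Group size: N = 30 to 40 in roughly equal HbA1c groups (Recruitment and Sampling), so 30/2 = 15 to 40/2 = 20 per group.
- Effect sizes: the article gives none. Differences of 0.5 and 0.8 SD are assumed for illustration.

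The article gives no power figure for these tests, so there is none to reproduce.

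**Step 1: match scales to directions**

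| Baseline instrument in Table 1 | Anticipated direction for HbA1c above 9% |
|---|---|
| Diabetes Adolescent Problem-Solving Questionnaire | lower |
| Diabetes Management Questionnaire (self-management) | lower |
| Problem areas in diabetes, teen version (distress) | higher |
| Patient Health Questionnaire, 2 items (depression) | higher |
| Self-efficacy for T1D management | none stated |
| CGM self-efficacy | none stated |
| Diabetes Technology Attitudes Scale | none stated |
| Benefits and burdens of CGM | none stated |

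Four of eight have a direction. Device use also has one, but it is a survey item and not one of these eight scales. Table 1 shows selected measures, so eight is the count on view and may not be the full count. If benefits and burdens are scored separately, five of nine lack a direction.

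**Step 2: error rate if the tail follows the data**

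Under no difference, a one-tailed test rejects with probability 0.05 in its own tail. If the tail is taken from the sign of the observed difference, it rejects in either tail: 0.05 + 0.05 = 0.10 per test. With a direction fixed beforehand, it stays at 0.05.

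**Step 3: chance of declaring a real difference opposite to the tested tail**

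With n per group and true difference d (in SD) in the other direction, the probability is 1 − F(t₀.₉₅; df = 2n − 2, noncentrality = −d√(n/2)), where F is the noncentral t distribution.

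| n per group | critical t | d = 0.5 | d = 0.8 |
|---|---|---|---|
| 15 | 1.701 | 0.14% | 0.008% |
| 20 | 1.686 | 0.07% | 0.002% |

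A two-sided 5% test would detect the same 0.8 SD difference with probability 56% at 15 per group and 69% at 20.

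**Step 4: what two-sided testing costs in the expected direction**

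One-sided power is 1 − F(t₀.₉₅; 2n − 2, d√(n/2)). Two-sided power uses t₀.₉₇₅ and adds the negligible opposite tail.

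| n per group | power at d = 0.8, one-tailed | power at d = 0.8, two-sided | d with 80% power, one-tailed | d with 80% power, two-sided |
|---|---|---|---|---|
| 15 | 68.9% | 56.2% | 0.93 SD | 1.06 SD |
| 20 | 79.9% | 69.3% | 0.80 SD | 0.91 SD |

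**The case against.** The best defence is that these tests are minor and the article is condensed. The sample size rests on qualitative data sufficiency, and the quantitative measures serve mainly to describe the sample. The Results section lists expectations and does not claim to list every tested hypothesis; a fuller protocol or analysis plan could fix the remaining directions. A one-tailed test with a direction fixed in advance does hold 5%. All of this stands. It limits the claim to what this article states, and it means that post hoc choice of tail is a risk, not an established fact. It does not give the stated rule a direction for four scales, and it does not let the rule declare an opposite result on the others.

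A reader might infer more, but the documents do not support it:

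- **That one-tailed testing inflates the overall false-positive risk.** Eight independent tests at 5% give 1 − 0.95⁸ = 33.7% for at least one false positive, but this is the same for two-sided tests. It is a multiplicity figure, it falls when scales are correlated, and a multiplicity rule may sit in an analysis plan that is not shown.
- **That greater device use in the ≤9% group could not be declared.** That is the anticipated direction, so the test can declare it.
- **That the article's remarks on discordant results argue against one tail.** Under Mixed Methods Integration, concordance means agreement between qualitative and quantitative findings, not agreement with a predicted sign.
- **That significant results drive the joint displays and the theory.** Those displays use survey scores and CGM summaries, and no significance threshold is described. A difference of unexpected sign would still be visible descriptively.

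**Conclusion.** The point holds in a limited form. As stated, the one-tailed rule has no defined tail for four of the eight scales shown. On each of those, a tail chosen from the data would give a 10% error rate in place of 5%. On the four directed scales, a true opposite difference of 0.5 to 0.8 SD would be declared significant with probability of about 0.1% or less. These figures assume normal scores, equal variances and 15 to 20 per group; the effect sizes are illustrative. The count of four rests on Table 1 and the Results section alone. The consequence is moderate: the comparisons support a qualitative primary aim, and the remedy is a change of wording.

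**What to change.** In Quantitative Analysis, replace the one-tailed tests with two-sided tests at α=.05 for all baseline comparisons between HbA1c groups. Report each mean difference with its 95% CI, and label the comparisons exploratory. The anticipated directions can stay in the Results section as expectations.

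Adding a direction for each remaining scale would make the tests defined but is the weaker remedy. It would still bar opposite findings, and 25 participants had enrolled by December 2025, so baseline scores may already be available when the directions are chosen.

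The cost is the power loss in Step 4: roughly 11 to 13 percentage points for a 0.8 SD difference. This is tolerable because the sample size was not set to power these tests, and the intervals will show how imprecise each comparison is. No change to data collection is needed.
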